10.4. Restrictions on the subjects (precautions)

(1) Take 2 capsules of the trial product after each meal every day during the consumption period of the trial, and record this in a journal.

(2) During the trial, maintain lifestyle habits from before the trial in areas such as diet, alcohol consumption, exercise, and sleep. Avoid large deviations from the normal range for exercise and food consumption (both under and over-eating).

(3) Do not consume any new health foods or supplements during the trial.

(4) Do not drink alcohol the day before or the day of examination, until the examination is over.

(5) Do not wear contact lenses the day before or the day of examination, until the examination is over. Bring the same glasses worn for the preliminary examination to each subsequent examination.

(6) Finish designated meals 2 hours before coming to the clinic on examination days (water can be consumed).

(7) Do not smoke for at least 2 hours before coming to the clinic on examination days.

**11. Expected side effects**

At present, no side effects are expected, although general symptoms from food (abdominal pain, diarrhea, other abdominal symptoms) could occur very rarely.

**12. Adverse events**

12.1. Definition of adverse events

Adverse events are defined as unwanted medical events that appear or worsen after consuming the trial product (subjective symptoms, objective signs, abnormal changes in examination values). There need not be a causal relationship with the trial product.

12.2. Assessment of adverse events

Adverse events that occur as subjective symptoms or objective signs will be assessed by the principal investigator. Whether abnormal changes in examination values should be considered adverse events will be determined by the principal investigator, based on the reference values of the trial institution and by referencing assessment criteria from the NCI, CTC, and Japanese Society of Chemotherapy (Chemotherapy. 2010.58 (4))

12.3. Collection and recording of adverse events

When an adverse event occurs, appropriate treatment will be administered as necessary. In addition, details about the symptoms and signs (diagnosis name), severity of adverse event, whether it is critical, has a relationship to the trial product, date of appearance, date of disappearance, whether the subject can continue the trial, whether hospital treatment was given (details of treatment), outcome, and comments by the physician will be recorded on the case report form. The date of appearance is defined as the date the adverse event appeared (if unable to determine, then record the date of confirmation), and the date of disappearance is the date the adverse event disappeared (if unable to determine, date of confirmation; if it does not disappear, date the outcome was confirmed).

Adverse events will be assessed according to the following criteria.

(1) Severity

Mild: Does not disturb daily life

Moderate: Disturbs daily life

Severe: Makes daily life almost impossible

(2) Critical adverse events

If an adverse event falls under any of the following criteria, it will be considered critical.

Death

An event that could lead to death (life-threatening event)

Events that require hospitalization for treatment, or that prolong a hospitalization

Causes disability (events that cause dysfunctions that inhibit daily activities)

Events that could lead to disability

Critical events that conform to the events (disabilities) described above

Causes congenital disease or abnormalities in later generations

(3) Relationship to trial product

No: A cause that is clearly not the trial product can be identified

Probably no: No logical, chronological, or medical connection can be established with consumption of the trial product

Possibly yes: A logical, chronological, or medical connection can be established with consumption of the trial product, but other causes are also suspected

Yes: A clear logical, chronological, or medical connection can be established with consumption of the trial product, and no other cause is suspected

(4) Outcomes

Recovery, disappearance: Symptoms or findings disappear; examination values normalize or return to pre-consumption levels

Recession: Severity decreases by 1 grade or more, mild symptoms or findings nearly disappear, examination values normalize or recover to near pre-consumption levels

- - 1. No change: Nearly no change in symptoms, findings, or examination values
       1. Aggravation: Symptoms, findings, or examination values worsen

Unclear: Following up on symptoms or examination values was attempted, but was unsuccessful (includes death) (example: change of address).

(5) Continuance of trial product intake

Continue: Continuing to take the trial product (continues the trial)

Suspension: Temporarily stopping trial product intake for observation

Termination: Stopping trial product intake

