**15. Evaluation methods**

15.1 Evaluating efficacy

(1) Primary outcomes: subjective dry eye symptoms, BUT, keratoconjunctival disorders, Schirmer’s test

(2) Secondary outcomes: functional vision

(3) Efficacy evaluation methods

For each item, values before consumption and at each time point after consumption will be compared between the trial group and the placebo group using a 2-sample t-test. The amount of change from before consumption to each time point after consumption will be compared between the trial group and the placebo group using a 2-sample t-test. Values at each time point after consumption will be compared to values before consumption in each group using a 1-sample t-test.

For the baseline characteristics of patients with dry eye, Student’s t-test (p ≥ 0.05 by the F-test) will be used for comparison of age, and Pearson chi-square test will be used for categorical data of gender and dry eye diagnosis. Repeated measures analysis of variance followed by Tukey's honest significant difference (HSD) post hoc test will be used for analysis of dry eye symptoms. For the biochemical analysis, paired t-tests will be used for within-group comparisons and the F-test, followed by Student’s t-test (p≥0.05 by the F-test) will be used for between-group comparisons (placebo vs. RJ). A p-value of <0.05 was considered statistically significant. 16.2. Evaluating safety

(1) Outcomes

These are adverse events confirmed from interviews and journal entries (subjective symptoms), and abnormal variations in body weight and scientific examination values. For examination values, changes in items will be checked: body weight, systolic blood pressure, diastolic blood pressure, heart rate, and biochemical data.

(2) Evaluation methods

The number of adverse events and abnormal variations will be totaled to create a table. If the same adverse event occurs in the same subject multiple times, it will be treated as one event. To evaluate changes in examination values, measurements before consumption and at each time point after consumption will be compared using a 1-sample t-test. Figures will be displayed as mean ± standard deviation (or standard error). The significance level will be 2-sided 5%.

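### The severity scale in 12.3(1) is defined only by disturbance of daily life, so a symptomless abnormal examination value is graded Mild whatever its size

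*Protocol*

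**What the plan says.** Four places in the protocol bear on this.

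- **Section 12.1** defines adverse events to cover "subjective symptoms, objective signs, abnormal changes in examination values", so a laboratory or vital-sign abnormality can be an adverse event without any symptom.
- **Section 12.2** hands one question to the investigator: "Whether abnormal changes in examination values should be considered adverse events will be determined by the principal investigator". The decision uses the institution's reference values and is made "by referencing assessment criteria from the NCI, CTC, and Japanese Society of Chemotherapy".
- **Section 12.3** lists severity among the items to enter on the case report form and then states, with no exception, "Adverse events will be assessed according to the following criteria". The severity grades are "Mild: Does not disturb daily life", "Moderate: Disturbs daily life" and "Severe: Makes daily life almost impossible".
- **Section 16.2, Evaluating safety** (printed at the end of section 15.1) brings examination values into the safety outcomes: "For examination values, changes in items will be checked: body weight, systolic blood pressure, diastolic blood pressure, heart rate, and biochemical data".

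**The concern.** Severity is meant to tell a reader how serious the recorded events were. A scale based on daily life does this for symptoms. For a laboratory value or a blood pressure reading that the subject cannot feel, it measures something the event does not affect. The grade is then fixed by the absence of symptoms, and the size of the abnormality plays no part.

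What is at stake is the meaning of the severity data for examination-value events. If the trial later reported that all adverse events were mild, that statement would, for symptomless abnormal values, follow from the scale and not from the data. A later analysis plan could not recover a magnitude grade from the severity field, because none would have been entered at the site.

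**Working it through.** The plan gives no figure to reproduce, so the check sets the definitions side by side and applies them.

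**1. Is an abnormal value within the scope of the scale?** Yes. 12.1 includes it among adverse events, and 12.3 applies its criteria to adverse events without setting examination values apart.

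**2. Do the criteria cited in 12.2 supply a grade?** Not as written. The sentence attaches them to the yes-or-no question of whether a change is an adverse event. Severity is first dealt with in 12.3, which brings its own scale and does not refer back to 12.2.

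**3. Apply the scale.** Take two subjects whose abnormal liver enzyme values are both judged to be adverse events and who have no symptoms.

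| | Subject A | Subject B |
|---|---|---|
| Size of abnormality | just enough to be called an adverse event | many-fold rise |
| Daily life disturbed? | no | no |
| Meets Mild | yes | yes |
| Meets Moderate | no | no |
| Meets Severe | no | no |
| Recorded severity | Mild | Mild |

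The result follows from the definitions; it is not an estimate of how often such events occur.

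**4. How many items are exposed?** Section 10.3 lists these analytes: total protein, AST, ALT, LDH, ALP, GGT, urea nitrogen, creatine (as printed), uric acid, total cholesterol, LDL cholesterol, HDL cholesterol, triglyceride, glucose and HbA1c. That makes 15. Section 16.2 adds body weight, systolic pressure, diastolic pressure and heart rate, which makes 4. Total: 15 + 4 = 19 items. This counts where the problem can arise, not how many events would be affected.

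**5. What else uses the grade?**

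| Element | Depends on the severity grade? |
|---|---|
| Critical classification, 12.3(2) | No; it has its own list of criteria |
| Outcome Recession, 12.3(4) | Partly; one route is a drop of a grade, but another refers directly to examination values |
| Other outcomes, 12.3(4) | No; Recovery, No change and Aggravation each name examination values, and Unclear concerns failed follow-up |
| Follow-up, 12.5 | No |
| Reporting, 12.6 | No; it depends on critical status |
| Stopping a subject, 13.2 | No severity grade is named |
| Safety tables and tests, 16.2 | No; events and abnormal variations are counted, and changes are tested |

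For a symptomless abnormal value already at the lowest of three grades, the grade-drop route to Recession is closed. The examination-value route stays open, so that outcome can still be recorded.

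**The case against.** The strongest reply is that little hangs on this field. No stated analysis tabulates events by severity, and no stated decision rule uses it. A dangerous but symptomless value can still be flagged as critical. The case report form also carries the diagnosis, the outcome, any treatment and the physician's comments, and the measured values are collected. All of this stands, and it sets the limit of the point.

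A second reply is that a scale of functional impact is a coherent choice, and that the investigator already has magnitude criteria in hand under 12.2. The first half is fair for symptoms. The second half does not close the gap, because 12.2 stops at whether a value is an adverse event. The outcome scale in 12.3(4) does provide for examination values, while the severity scale beside it has no counterpart.

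Three stronger readings are tempting, and the protocol supports none of them:

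- *That severity drives follow-up or continuation.* Sections 12.3(5), 12.5, 12.6 and 13.2 make no such link.
- *That the outcome scale fails as well.* Recession has its own wording for mild findings and for examination values.
- *That a laboratory signal would be hidden.* The counts and the tests of change in 16.2 do not involve the grade. Those tests summarise groups, and under 14.2(2) they cover only subjects who complete the schedule, so they do not grade an individual's abnormality. That makes the severity field worth repairing; it does not mean the data are lost.

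**Conclusion.** The point holds in a limited form. The protocol states a rule that gives an uninformative severity grade to symptomless abnormal examination values, across up to 19 monitored items. The severity field cannot separate a trivial abnormality from a marked one, and any severity statement that includes such events inherits this. Nothing else in the planned safety evaluation changes.

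The weight is minor to moderate. The conclusion assumes that sites apply 12.3(1) as written and that the 12.2 criteria are used only for the purpose that section gives them. The protocol offers no basis for estimating how many events would be affected.

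**What to change.** In 12.3(1):

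- State that the daily-life scale applies to symptoms and signs.
- State that adverse events arising from examination values are graded with one named set of the criteria already cited in 12.2.
- In 16.2, report those events by that grade.

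The Recession definition needs no change.

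The protocol does not reproduce the cited criteria. The fix therefore assumes that the chosen set grades by size of abnormality and covers the monitored items. This should be checked when the set is named, and the protocol should say how any uncovered item is graded.

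The cost is about one paragraph in 12.3, a reporting line in 16.2 and one case report form instruction, with no new measurement. The downside is that some events now called mild will be reported at a higher grade.

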12.4. Side effects

Side effects are adverse events that are determined to have or possibly have a relationship with the trial product, and for which a causal relationship with the trial product cannot be ruled out.

12.5. Follow-up examinations

When an adverse event occurs, follow up examinations will be conducted until the event disappears, a recovery trend is observed, or the principal investigator decides they are no longer necessary.

12.6. Reporting procedure when critical adverse events occur

If an adverse event is determined to be critical, the principal investigator will notify the chief of the trial institution soon after it is discovered. A report on the critical adverse event will be made and submitted to the chief of the trial institution.

**13. Termination and dropping out**

13.1 Definitions

Termination when the primary investigator decides to discontinue the trial before it is completed. Dropping out is defined as when a subject decides to discontinue the trial due to circumstances or his/her desire before the trial is completed.

13.2. Termination

If any of the following events occur, the primary investigator can discontinue a particular subject’s participation in the trial or the entire trial.

(1) Termination of a particular subject

If a subject’s safety could be at risk

If a critical clinical abnormality or accident occurs that makes continuing the trial difficult

If the subject makes serious or continuous infringements to the trial protocol

If the principal investigator decides, the trial should be terminated for any other reason

(2) Terminating the trial

If the trial sponsor needs to terminate the entire trial for some reason, the sponsor will cooperate with the contract research organizations to determine a plan for ending the trial and for what will occur afterwards. The sponsor will quickly notify in writing the primary investigator, ethics committee, and trial institution that the trial is being terminated and the reasons for this.

If the principal investigator is notified that the entire trial will be terminated, or if information is obtained that could affect a subject’s continued participation in the trial, the subjects will be provided with this information.

If the ethics committee requests anything after the trial is terminated, the trial sponsor will work with the contract research organizations and principal investigator to address this request.

13.3. Dropping out

If a subject, after agreeing to participate in the trial, decides to drop out due to circumstances or his/her desire, the principal investigator will terminate the subject’s participation in the trial.

13.4. Dealing with terminations (dropouts)

In the event of a termination (dropout), the date and reason for the termination (dropout) will be recorded in the case report form.

**14. Selecting the analysis set**

14.1. Efficacy analysis set

The analysis set will comprise subjects who complete all of the trial’s designated schedule and content, and exclude those who fall under the following criteria:

[Criteria for exclusion from the analysis set]

(1) Consuming less than 80% of the trial product

(2) Behavior that could harm the reliability of the results, such as missing journal entries

(3) Discovery that a subject falls under the exclusion criteria after he/she is included in the trial, or that a subject violated the restrictions (precautions) during the trial

(4) Other reasons that make exclusion appropriate

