4.3. Functional ingredient: RJ

4.4. Composition of trial product

| Per capsule  (approximate value) | | Trial product* | Placebo |
| --- | --- | --- | --- |
| Calories | (kcal) | 2.2 | 2.03 |
| Protein | (g) | 0.16 | 0.15x10-3 |
| Fat | (g) | 0.03 | 0.025 |
| Carbohydrates | (g) | 0.31 | 0.43 |
| Sodium | (mg) | 9.43 | 0.045 |

* Each capsule contains 1,200 mg enzyme-treated RJ (raw product)

4.5. Determination of trial product intake, method of consumption, period of consumption, functional ingredient intake.

(1) Trial product intake, method of consumption.

Two capsules are to be taken unchewed with water after meals, 3 times per day. If subjects forget to take capsules after meals, they can take 6 capsules at one time on that day. Capsules for multiple days should not be taken together. Subjects will record the times and amounts taken in daily journal entries. If they forget to take capsules, this should be recorded in that day’s entry. The subjects should not take any capsules before coming to the clinic on examination days. They can take capsules after the examinations for the fourth week and beyond.

(2) Period of consumption of the trial product.

The period will be 8 weeks (56 days).

(3) Basis for determining functional ingredient intake.

Consumption of 3 to 6 capsules of the RJ product per day was used as a benchmark, with each capsule containing 1,200 g of enzyme-treated RJ (raw product). Clear effects were observed in animal experiments at 300 mg/day, so daily intake for this trial was set at 6 capsules (equivalent to 7,200 mg). Daily intake was also determined based on amounts that were confirmed to be safe in multiple past trials involving other RJ-related products.

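### The only efficacy set is compliant completers with open-ended exclusions, so the group comparisons are not protected by randomisation, and the rules for membership do not fit together

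*Protocol*

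**What the plan says.** Section 14.1 opens with "The analysis set will comprise subjects who complete all of the trial’s designated schedule and content" and then removes four groups:

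- (1) "Consuming less than 80% of the trial product".
- (2) "Behavior that could harm the reliability of the results, such as missing journal entries". No number of entries is given.
- (3) Subjects later found to meet an exclusion criterion, "or that a subject violated the restrictions (precautions) during the trial". No degree of violation is given.
- (4) A residual clause for any other reason judged to justify exclusion.

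No other efficacy set appears in the protocol. Section 15.1 runs 2-sample t-tests between the groups on values and on changes.

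Three other sections decide who is in the set. The heading of 10.4 names the restrictions (precautions) that 14.1(3) invokes, and its first item is "Take 2 capsules of the trial product after each meal every day during the consumption period of the trial, and record this in a journal". Section 4.5(1) allows something different: "If subjects forget to take capsules after meals, they can take 6 capsules at one time on that day". It also tells subjects to note forgotten capsules in the journal. When a subject decides to drop out, 13.3 says that "the principal investigator will terminate the subject’s participation in the trial", and 13.4 asks only for the date and reason.

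Section 6.2 contains one safeguard: the allocation table is unsealed only after the analysis set and the data are fixed.

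**The concern.** Completing the visits, taking the capsules, keeping the journal and respecting the restrictions all happen after allotment. Each can depend on how a subject tolerates the product or whether symptoms improve. A comparison restricted to subjects selected in this way is not the comparison that randomisation set up, and every efficacy conclusion in the protocol would rest on it.

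The membership rules make this worse because they leave room for discretion. Two analysts who apply 14.1 in good faith could produce quite different sets, one keeping a subject with 85% intake and the other removing a subject with one missed dose. With 25 subjects per group at the start of consumption, moving a few subjects in or out can change a result.

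**Working it through.** **1. The protocol's own figures.** No effect size, SD, power or dropout rate is stated, so there is no power figure to reproduce. The simple counts agree: 2 x 25 = 50 subjects; 2 capsules x 3 times = 6 per day; 6 x 56 days = 336 capsules; 3 x 56 = 168 intake occasions.

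**2. The intake rules side by side.**

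| Rule | Intake needed to stay in the set | Capsules that may be missed |
|---|---|---|
| 14.1(1) | 0.80 x 336 = 268.8, so at least 269 | 336 - 269 = 67 (about 11 days) |
| 14.1(3) with 10.4(1), read literally | all 336, two after each meal | 0 |
| 4.5(1) | same-day catch-up of 6 at once is allowed | the subject takes 336 of 336 but departs from 10.4(1) |

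Read literally, the second row leaves the first with no effect of its own.

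**3. How far apart the two readings are.** Assume that each occasion is missed independently with probability p. The chance of no miss in 168 occasions is (1 - p)^168.

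| Assumed p | No miss at all | Meets the 80% rule |
|---|---|---|
| 0.1% | 85% | essentially 100% |
| 0.5% | 43% | essentially 100% |
| 1% | 18% | essentially 100% |
| 2% | 3% | essentially 100% |

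**4. Completing all content is not determinate.** The schedule table marks Schirmer's test at every visit, including Week 4, and 10.1(5) lists it for Weeks 4 and 8. The third footnote in 10.3 places it at the preliminary and eighth-week examinations only. Whether a subject without a Week 4 Schirmer's value is a completer depends on which text is used.

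**5. Possible bias (assumed illustration).** Take 25 per arm, a normal outcome with SD 1, no true effect and a two-sided 5% t-test. A subject with an average outcome is excluded with probability 20%. The log-odds of exclusion rise by the slope shown for each SD of worse outcome. In an arm with slope 0, exclusion is random at 20%.

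| Slope, product arm | Slope, placebo arm | Excluded, product arm | Bias (SD) | Type I error |
|---|---|---|---|---|
| 0 | 0 | 20% | 0.00 | 5% |
| 0.5 | 0 | 21% | 0.10-0.11 | 6% |
| 1 | 0 | 24% | 0.20-0.21 | 10% |
| 1.5 | 0 | 27% | 0.30 | 15-16% |
| 1 | 1 | 24% | 0.00 | 5% |
| 0 | 1 | 20% | -0.20 | not computed |

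Ranges cover repeated runs. With a base rate of 5% and slope 1 in the product arm only, bias is 0.07 SD and type I error 5.5%.

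**6. Cost in precision.** By the normal approximation, the difference detectable with 80% power is (1.96 + 0.84) x sqrt(2/n) SD: 0.79 at n = 25 per arm, 0.89 at 20 and 1.02 at 15. For an assumed effect of 0.8 SD, power is 81%, 72% and 59% respectively.

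**The case against.** The strongest defence is that the trial is double-blind and 6.2 fixes the set before unsealing. Selection then distorts the comparison only if exclusions relate to outcome differently in the two arms, and nothing in the protocol shows that they will. This is right as far as it goes, and it rules out four stronger readings:

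- *Randomisation is broken.* A reader might infer this. The text supports only that the comparison is no longer protected; with the same exclusion mechanism in both arms the illustrated bias is about zero.
- *The bias favours the product.* Poor responders could equally leave the placebo arm, which reverses the sign. Section 11 expects no side effects and calls abdominal symptoms very rare.
- *One blank journal day, or use of the catch-up allowance, removes a subject.* Criterion (2) is a judgement about reliability, and an act that 4.5(1) permits is not naturally a violation. The defect is that the text does not settle either case. The ban in 4.5(1) on capsules before examination visits is likewise best read as a specific exception to 10.4(1).
- *The number analysed will fall below a planned 25 per group.* Sections 1 and 6.1 set 25 at the start of consumption only.

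It can also be said that an SAP may add further sets. But 14.1 does not leave the matter open: it states the efficacy set and makes it a completer set. Blinding also does not remove selection that arises because completion or adherence depends on the product, nor does it say which intake rule governs.

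**Conclusion.** The point holds, in measured form. Section 14.1 commits every efficacy comparison to a set chosen mainly on post-randomisation events, with two criteria, (2) and (4), that have no threshold. Criterion (3) read with 10.4(1) undercuts both the 80% rule and the catch-up in 4.5(1).

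The gap between the rules is a matter of text: 67 missed capsules against none. The bias is not. Its direction and size are unknown, and the figures of 0.2-0.3 SD and 10-16% type I error hold only for assumed outcome-related exclusion of about 24-27% in one arm. The miss rates and the 0.8 SD effect are assumptions too. Even so, this is worth fixing before the data are analysed, because all efficacy conclusions depend on this set and the repair is cheap.

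**What to change.** 1. Make the primary efficacy set all randomised subjects with available post-baseline data, analysed as allotted, using all available Week 4 and Week 8 values. Requiring post-baseline data is itself a mild selection, so report the number lost in each arm and why.
2. State in section 13 that subjects who stop the product without withdrawing consent are still asked to attend the examinations already scheduled.
3. Keep 14.1 as a per-protocol sensitivity set. Remove criteria (2) and (4), or give them objective thresholds set before unsealing.
4. Reconcile 14.1(1), 14.1(3), 10.4(1) and 4.5(1), so that it is clear what counts as a violation for analysis purposes. Which intake rule should stand is for the sponsor and investigator.
5. Reconcile the Schirmer's test timing in the schedule table, 10.1 and 10.3, so that completion of the designated content can be decided for each subject.

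The cost is amendment wording and a few visits that are already in the schedule. The downside is some dilution of the estimated effect by non-compliers; the per-protocol analysis lets readers see the result without them.
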